| The primary objective of the Randomised Controlled Trial is to determine the effectiveness of a tailored structured community exercise programme in improving functional outcomes in older adults with a high risk of falls. The primary outcome of interest would be the difference in Short Performance Physical Battery (SPPB) scores between the intervention and control groups at 6 months. It is hypothesized that the intervention group will show ≥ 0.6 points improvements in SPPB scores compared to the control group.  Part 2 secondary objectives are to:   1. Evaluate the effect of the exercise programme on balance confidence 2. Evaluate the effect of the exercise programme on fear of falling 3. Evaluate the effect of the exercise programme on participants’ quality of life 4. Evaluate the effect of the exercise programme on falls rates 5. Evaluate the effect of the exercise programme on healthcare cost 6. Evaluate the adoption of the exercise programme 7. Understand the factors contributing to long-term sustainability of SF for further development and implementation 8. Evaluate the programme’s reach and fidelity |
|  |
| **EXPECTED RIKS AND BENEFITS** |
| There is a slight risk of injuries during the exercise classes. However, all necessary precautions will be taken to minimize this risk and all exercises are supervised by trained personnel. Potential benefits include improved strength, and balance. |
| **STUDY POPULATION** |
| List the number and nature of subjects to be enrolled. |
| The RCT will enrol 260 community-dwelling older adults aged 60 years and above who meet the study’s eligibility criteria, of which, a subset of them will be offered to participate in a qualitative interviews/FGDs to determine the implementation outcome of SF and to understand factors contributing to long-term sustainability of SF for further development and implementation. |
| Criteria for Recruitment and Recruitment Process |

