| Serious adverse event (SAE) in relation to human biomedical research, means any untoward medical occurrence as a result of any human biomedical research which:   - results in or contributes to death - is life-threatening - requires in-patient hospitalisation or prolongation of existing hospitalisation - results in or contributes to persistent or significant disability/incapacity or - results in or contributes to a congenital anomaly/birth defect - results in such other events as may be prescribed   Adverse event (AE) in relation to human biomedical research means any untoward medical occurrence as a result of any human biomedical research which is NOT serious. Adverse event can be any unfavourable and unintended sign (including an abnormal laboratory finding), symptom, or disease possibly/ probably/ definitely associated with the participant in the human biomedical research. |
| Collecting, Recording and Reporting of Serious Adverse Events (SAEs) to CIRB |
| Only related SAEs (definitely/ probably/ possibly) will be reported to CIRB. Related means there is a reasonable possibility that the event may have been caused by participation in the research. Please refer to the CIRB website for more information on Reporting Requirement and Timeline for Serious Adverse Events.  The investigator is responsible for informing CIRB after first knowledge that the case qualifies for reporting. Follow-up information will be actively sought and submitted as it becomes available.  Related AEs will not be reported to CIRB. However, the investigator is responsible to keep record of such AEs cases at the Study Site File. |
| Safety Monitoring Plan |
| The study team will conduct, at least, quarterly meeting to review the study data. Study data to be reviewed will include compilation of data obtained from study and any adverse events and/or serious adverse events recorded to ensure that patient safety is adhered. |
| Complaint Handling |
| Any participant complains will be raised to the PI and dealt with on a case-by-case basis. |
| **DATA ANALYSIS** |
| Data Quality Assurance |
| Data will be routinely reviewed for the purposes of tracking the progress of the study, assuring accuracy, and completeness of the data. Adverse events or serious adverse events will be recorded and monitored to ensure the safety of the participants. |
| Data Entry and Storage |

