| Data will be collected via 1) hard copy data collection forms and/or 2) extracted electronically from hospital clinical systems, and/or 3) digital audio recorders. Data will be entered into an electronic database, and together with audio recordings will be stored on a password protected laptop accessible only to the PI, Co-Investigators and study team members. |
| **SAMPLE SIZE AND STATISTICAL METHODS** |
| Determination of Sample Size |
| The primary outcome for the study is the difference in SPPB scores between intervention and control group at 6 months.  We estimated a predicted effect size of around 0.4, at 80% power using a two-sided 0.05 level t-test. Accounting for an attrition rate of around 25%, an estimated sample size of 130 participants per group was obtained. Sample size calculations were calculated with G*Power (ver. 3.1.9.4).  An adaptive design may be used after the interim analysis. Sample size re-estimation may be performed to evaluate the power to detect a statistically significant difference in primary outcome between the intervention group and the control group based on an interim analysis. |

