| Statistical and Analytical Plans **Statistical and Analytical Plans**  Data Sets to Be Analyzed  The primary analysis will include all available data from all participants who were randomized into the intervention or control groups. This is the intention to treat data set.  Analysis of Variable(s)  RCT analysis will accord with the “intention-to-treat” principle. A *p* < 0.05 will be considered as statistically significant.  Categorical data will be presented as frequency (percentage), while continuous data will be presented as mean (standard deviation) for parametric distribution and median (interquartile range) for non-parametric distribution. Group or pre/post comparisons of categorical and continuous variables will be performed using chi-square test/ Fisher’s Exact test and/or ANOVA as appropriate.  Categorical variables might be examined using logistics regression models. Demographics and baseline variables will be examined between groups and might be used for adjustment of the regression models. The between group differences in primary and secondary outcomes will be examined using regression and/or ANOVA models.  Cost analysis will examine total healthcare cost from primary care to acute hospital stays during the study period.  If data transformations (e.g., logarithmic) are used to improve distribution characteristics (e.g., normality, variance homogeneity) for parametric procedures, they will be described in reporting of statistical results.  Audio recordings will be transcribed verbatim, translated if needed, and then analysed using content or thematic analysis.  Interim Analysis Plan  An interim analysis might be conducted when approximately 70 participants per group have a known 6^th^ month primary outcome.  Criteria for Early Termination of the Trial  After the interim analysis, sample size and study power might be re-estimated. There are no plans to terminate the trial early. |
|  |
| **DIRECT ACCESS TO SOURCE DATA/DOCUMENTS** |
| The investigator(s)/institution(s) will permit study-related monitoring, audits and/or IRB review and regulatory inspection(s), providing direct access to source data/document. |
|  |
| **QUALITY CONTROL AND QUALITY ASSURANCE** |

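### The protocol allows an interim sample size re-estimation with no rule, cap or blinding, then a flat p < 0.05, so the two-sided 5% level is not guaranteed

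*Protocol*

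**What the plan says.** Under Determination of Sample Size, the protocol plans 130 per group for a standardised effect of about 0.4 "at 80% power using a two-sided 0.05 level t-test", with about 25% attrition. It then says that an adaptive design may follow the interim analysis: "Sample size re-estimation may be performed to evaluate the power to detect a statistically significant difference in primary outcome" between the two groups, on the basis of that analysis.

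The Interim Analysis Plan sets the timing: "An interim analysis might be conducted when approximately 70 participants per group have a known" 6-month primary outcome. Criteria for Early Termination adds that size and power might be re-estimated afterwards and that no early termination is planned. Under Analysis of Variable(s), the only criterion is that p below "0.05 will be considered as statistically significant".

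The protocol does not say whether the review is blinded, how the new size is set, how large it may become, or whether the final test takes account of the change. It gives no recruitment rate or duration.

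**The concern.** If the interim effect influences how many more participants are recruited, the ordinary pooled test statistic no longer has its nominal distribution under the null. With a weak interim result, a larger second stage gives chance more room to carry the total past 1.96. With a strong one, a small second stage protects the lead. Testing at a plain 0.05 afterwards can then reject too often. This affects the primary endpoint: a result near p = 0.05 after such a re-estimation would be hard to defend at the stated level, and a rule written after the look could not credibly be called pre-specified.

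The second worry is practical. A look that waits for 140 six-month outcomes may arrive when recruitment to the planned 260 is finished or nearly so.

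**Working it through.** **1. The planned size.** Inputs from the protocol: effect 0.4, two-sided 0.05, power 80%, attrition 25%.

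n = 2(1.96 + 0.84)² / 0.4² ≈ 98, or 99 once rounded up from unrounded quantiles; 99 / 0.75 = 132 per group. This agrees with 130, given that both inputs are stated as approximate. Conversely, 130 × 0.75 = 97.5, so about 98 evaluable per group are expected and the interim falls at 70/98 = 71% of them.

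**2. Type I error after re-sizing on the observed effect.** The rule is an assumption, since the protocol gives none. Let Z1 be the interim statistic at 70 per group and d = |Z1|√(2/70). The new size is n = 2(1.96 + 0.84)² / d², clipped to an allowed range. The final test rejects if

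|√(70/n) Z1 + √((n − 70)/n) Z2| > 1.96,

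where Z2 is the independent second-stage statistic. Integrating over Z1 under the null gives:

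| Rule | Range of n per group | Type I error |
|---|---|---|
| No change | 98 | 5.0% |
| Increase only, cap 1.5× | 98 to 147 | 5.7% |
| Increase only, cap 2× | 98 to 196 | 6.1% |
| Increase or decrease, cap 2× | 70 to 196 | 6.4% |
| Worst increase-only choice, cap 1.5× | 98 to 147 | 6.1% |
| Worst increase-only choice, cap 2× | 98 to 196 | 6.7% |

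The worst-choice rows take, for each Z1, the n in the range that maximises the chance of rejection. No other increase-only rule with the same cap can exceed them.

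**3. Rules that do no harm.** Increasing n only when conditional power at the interim is at least 50% (a promising-zone rule) gives about 4.8%. Blinded re-estimation from the pooled SD gives about 5.1% by simulation.

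**4. Timing.** 140 outcomes at 25% attrition need 140 / 0.75 ≈ 187 participants randomised at least 6 months earlier. With uniform accrual of 260 over T months, enrolment at the look is 187 + 260 × 6/T. This reaches 260 when T = 260 × 6 / 73.3 ≈ 21 months, or about 12 participants a month. Using the full 30-day visit window (7 months) moves the limit to about 25 months. At 5 a month, about 187 + 30 = 217 would be enrolled.

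**The case against.** The text does not say that the review is unblinded or that the observed effect sets the new size. Power also depends on the SD and on attrition, and a blinded SD review would fit the wording. With no early stopping planned, the look by itself spends no alpha; only re-sizing does. The details may also stand in a separate SAP. All of this is fair, and it is why the 5% level can be called not guaranteed but not lost. What stands is that the protocol ties the re-estimation to power for the between-group difference, counts outcomes per group in an open-label trial, and states one unadjusted threshold. Whether that threshold holds depends on a choice left open until data are in hand.

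A reader might infer three stronger things that the documents do not support:

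- **That the error could approach 8% to 10%.** Such values need very large caps, or permission to cut the trial to near its interim size. Conditional-power rules that may also cut the size give 7.4% to 8.6%. Deep cuts are hardly available, because participants beyond the first 140 outcomes are already enrolled: at 10 a month, about 247 × 0.75 / 2 ≈ 93 evaluable per group.
- **That the look probably comes too late.** This depends on an accrual rate the protocol does not give, and a late look would not prevent an extension.
- **That the study team will be comparing arms every quarter.** "The study team will conduct, at least, quarterly meeting to review the study data" stands in the Safety Monitoring Plan with patient safety as its purpose, and it mentions no comparison of SPPB by arm.

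**Conclusion.** The point holds as a gap in error control, not as a demonstrated breach. As written, the protocol permits procedures whose two-sided type I error is about 5.7% to 6.1% for ordinary increase-only re-sizing, at worst 6.1% to 6.7% under the same caps, and about 6.4% when the size may also fall. It equally permits procedures that hold 5%. The figures assume an unblinded rule, an unadjusted pooled test, 70 per group at the interim and 98 planned. The inflation is modest, but it falls on the primary endpoint and can be avoided.

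Timing is secondary and conditional: the planned recruitment would already be complete at the look if it takes about 21 months or less at 25% attrition, and not if it is slower.

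**What to change.** Replace the adaptive wording in Determination of Sample Size, the Interim Analysis Plan and Criteria for Early Termination with a blinded re-estimation:

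- estimate the SPPB SD from the pooled data without arm labels;
- recompute n for the planned difference, allowing increases only;
- state a maximum n;
- keep the final two-sided 0.05 test.

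The protocol gives no SD. If its 0.6-point difference and its effect size of 0.4 belong together, the reference SD is 0.6/0.4 = 1.5, and the rule is n = 98 × (SD/1.5)² evaluable per group, never below 98. The reference value should be written down.

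If an unblinded look is kept, pre-specify the rule and the cap, and test with an inverse-normal combination, √(70/98) Z1 + √(28/98) Z2 = 0.845 Z1 + 0.535 Z2, against ±1.96. Z2 uses only outcomes not in the interim, and the weights stay fixed whatever the final n. The square roots matter: using 70/98 and 28/98 themselves against 1.96 would give a level of only about 1.1%.

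The cost is a protocol amendment notified to the CIRB, made before any interim look. The planned 260 stands unless the SD proves larger. The blinded route gives up an early view of the effect and cannot respond to an effect smaller than assumed.

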| **Randomised controlled trial; community-dwelling older adults at high risks of falls**   - To determine the effects of SF on functional outcomes   Control (*n* = 130)   - Education and advice on how to reduce your risk of falls   Intervention (*n* = 130)   - 6-months exercise programme - Education and advice on how to reduce your risk of falls   A study comprising of (i) an open-label, parallel randomized controlled trial, and (ii) qualitative interviews or focus group discussions will be performed to assess the aims of the study. Crucial implementation outcomes, including reach, and fidelity, will also be collected.  Based on sample size calculations for the RCT (details can be found in Section 8), the study will involve 260 older adults aged 60 years and above who are at high risk of falls, and a subset will be recruited for the qualitative interviews/discussions.  After enrolment into the study, allocation concealment will be used to randomize participants to the intervention or control group before the baseline visit. Participants will be followed up prospectively for the next 6 months.  Participants will undergo the following activities.  **Intervention Group**:   - Attend 3 evaluation assessments during the study period. - Participate in 6 months of exercises   The exercises are divided into 2 phases:   - The Steady Feet (SF) exercise programme phase. A twice weekly tailored structured group exercise class that will be conducted for 3 months with community instructors and exercise video. - A 3 months maintenance exercise phase. A once weekly structured community group exercise class selected by participants from a recommended list of exercises [list is provided by the study team].   **Control Group**:   - Attend 3 evaluation assessments during the study period.   Primary Variable   - Functional assessment i.e. Short Physical Performance Battery (SPPB)   Secondary Variable(s)   - Balance confidence i.e. ConfBAL scale - Fear of Falling - Quality of life i.e. EQ-5D-5L - History of injurious falls - Single Leg Stance (SLS) - Four Square Step Test (FSST) - Timed Up and Go (TUG) - 30 second chair stand test (30CST) - 6-minute walk test (6MWT) - Healthcare utilisation - Cost of healthcare utilisation - Competency level of community instructors   Socio-demographic variable(s) and other supportive variables   - Age, gender, ethnicity, marital status, education level, residential type - Anthropometric measurement: weight and height - Measure of co-morbidities, i.e. Charlson Comorbidity Index (CCI) - Physical activity levels i.e. Global Physical Activity Questionnaire (GPAQ) - Satisfaction and open-ended feedback of community providers and instructors - Satisfaction and open-ended feedback of participants - Borg Rate of Perceived Exertion (RPE) - Attendance rate of exercise classes - Uptake rate of community-based exercises   **Study procedures and Visit Schedule**  Randomised controlled trial:  For intervention group:  Participants will take part in 6 months of community-based exercises that will commence within 2 weeks from the baseline visit.   \| Visit \| Visit 1  Baseline^1^  Day 1 \| Visit 2  3-month  Day 90 + 30 days^2^ \| Visit 3  6-month  Day 180 + 30 days \| \| --- \| --- \| --- \| --- \| \| Evaluation assessment visit procedures \| - Functional assessments - Questions on:   - Physical Activity levels   - Confidence balance   - Quality of Life   - History of injurious falls \| - Functional assessments - Questions on:   - Physical Activity levels   - Confidence balance   - Quality of Life   - Healthcare utilisation and related costs   - Programme satisfaction \| - Functional assessments - Questions on:   - Physical Activity levels   - Confidence balance   - Quality of Life   - History of injurious falls   - Healthcare utilisation and related costs   - Programme satisfaction \|   For controls:   \| Visit \| Visit 1  Baseline^1^  Day 1 \| Visit 2  3-month  Day 90 + 30 days \| Visit 3  6-month  Day 180 + 30 days \| \| --- \| --- \| --- \| --- \| \| Evaluation assessment visit procedures \| - Functional assessments - Questions on:   - Physical Activity levels   - Confidence balance   - Quality of Life   - History of injurious falls \| - Functional assessments - Questions on:   - Physical Activity levels   - Confidence balance   - Quality of Life   - Healthcare utilisation and related costs \| - Functional assessments - Questions on:   - Physical Activity levels   - Confidence balance   - Quality of Life   - History of injurious falls   - Healthcare utilisation and related costs \|   ^1^Baseline visit will take place within 50 days from the screening, and within 2 weeks prior to the commencement of the intervention group’s exercise classes.  ^2^Visit 2 will be conducted on a separate day after the last scheduled exercise class has been completed.  Participation in the RCT study is voluntary in nature. Participants may withdraw from participation in the study at any time by informing the study team members. However, data that have been collected until the time of participant’s withdrawal will be kept and analysed.  Qualitative interviews or focus group discussions:  Participation in the qualitative interviews/discussions is voluntary in nature, and the purpose of this portion is to better understand the factors contributing to long-term sustainability of Steady Feet for further development and implementation. The interviews or focus group discussions will be audio-recorded, and participants can request to remove what they mentioned during the sessions. The sessions are expected to last no longer than 2 hours. |

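### Categorical pre/post comparisons are assigned to chi-square or Fisher's exact tests, which ignore that the same participants are measured twice; the type of ANOVA for continuous pre/post data is left open (minor)

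*Protocol*

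**What the plan says.** In the protocol's Statistical and Analytical Plans, under Analysis of Variable(s), one sentence covers both comparisons between groups and comparisons over time: "Group or pre/post comparisons of categorical and continuous variables will be performed using chi-square test", with Fisher's exact test and/or ANOVA as the other options, to be chosen as appropriate. A little later, a separate sentence covers the outcomes: "The between group differences in primary and secondary outcomes will be examined using regression and/or ANOVA models". The same subsection sets a single threshold of p < 0.05, which "will be considered as statistically significant", with no exemption for pre/post tests. It adds that categorical variables might be examined by logistic regression, without mentioning correlation within a person.

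The study design section has each arm "Attend 3 evaluation assessments during the study period". The Schedule of Data Collection (RCT) repeats the functional tests, ConfBAL, fear of falling and EQ-5D-5L at baseline, 3 and 6 months, and takes the history of injurious falls at baseline and 6 months.

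Under Determination of Sample Size, the primary outcome is a contrast between arms: "The primary outcome for the study is the difference in SPPB scores between intervention and control group at 6 months".

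**The concern.** A comparison between arms uses different people. A pre/post comparison uses the same people twice, so the two values are paired. Pearson's chi-square and Fisher's exact test both take the two sets of observations as independent. The phrase about appropriateness lets the analyst choose within the list, but the list holds no paired categorical test, and the protocol names none elsewhere.

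This goes beyond detail left to a statistical analysis plan. The protocol names the tests and assigns them to pre/post data. A later plan that used McNemar's test would be right, but it would depart from this sentence.

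What is at stake is the validity of categorical pre/post p-values. With positive within-person correlation the unpaired test uses too large a standard error, so real changes are more easily missed. A plausible case is the history of injurious falls at baseline and 6 months, if analysed as yes/no.

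**Working it through.** **The plan's own figure.** Inputs from Determination of Sample Size: "We estimated a predicted effect size of around 0.4, at 80% power using a two-sided 0.05 level t-test", and "Accounting for an attrition rate of around 25%, an estimated sample size of 130 participants per group was obtained".

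- n per arm = 2(1.96 + 0.842)² / 0.4² = 98.1, taken up to 99. Then 99 / 0.75 = 132, close to the stated 130.
- Forward check: 130 × 0.75 = 97.5 completers per arm gives power of 79.8% (normal) or 79.4% (t-test).

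The figure is reproduced closely enough. It rests on a two-group comparison, so the pairing question does not touch it.

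**Inputs for the pre/post check.** Completers in one arm: 97, from 130 × 0.75 = 97.5. Two-sided level: 0.05. The documents give neither a within-person correlation nor a size of pre/post change. Assumed here: correlation (ρ; phi for a binary item) of 0.3, 0.5 and 0.7, and a binary item falling from 40% to 28%.

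**Binary item, no true change.** The unpaired test uses a variance of 2p(1−p)/n. The variance of the paired difference is 2p(1−p)(1−ρ)/n. The unpaired standard error is therefore too large by 1/√(1−ρ), and the true type I error is about 2Φ(−1.96/√(1−ρ)):

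| ρ | 1/√(1−ρ) | True type I error of chi-square |
| --- | --- | --- |
| 0.3 | 1.20 | 1.9% |
| 0.5 | 1.41 | 0.6% |
| 0.7 | 1.83 | 0.03% |

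**Binary item, 40% to 28%.** The joint probability of yes at both times is p₁p₂ + φ√(p₁(1−p₁)p₂(1−p₂)). At φ = 0.5 this is 0.112 + 0.5 × 0.220 = 0.222. The discordant cells are then 0.40 − 0.222 = 0.178 and 0.28 − 0.222 = 0.058, together 0.236.

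- Chi-square: pooled proportion 0.34, standard error √(2 × 0.34 × 0.66 / 97) = 0.068, typical z = 0.12 / 0.068 = 1.76, below 1.96.
- McNemar: typical z = 0.12 × √97 / √0.236 = 2.43, above 1.96.

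Simulated power for all three correlations (repeat runs differ by up to about one percentage point):

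| φ | Chi-square | McNemar, uncorrected | McNemar, exact |
| --- | --- | --- | --- |
| 0.3 | 41% | 56% | 47% |
| 0.5 | 39% | 72% | 63% |
| 0.7 | 36% | 92% | 88% |

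**Continuous variables.** If, and only if, a between-subjects ANOVA were run on paired values, the standard error of the mean change would be too large by √2 / √(2(1−ρ)) = 1/√(1−ρ), again 1.20 / 1.41 / 1.83 times. A repeated-measures ANOVA has no such error. The protocol does not say which is meant.

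**The case against.** The strongest objection is that the sentence does not rule out a correct analysis. It says ANOVA without qualification, and for a pre/post comparison repeated-measures ANOVA is a natural reading. Most listed outcomes are scores, times, counts or distances, so they fall on that side. The exact ANOVA model is commonly left to the statistical analysis plan. This stands: a reader might infer that every pre/post p-value and confidence interval is wrong, and the document does not support that. For continuous data the method is unspecified, and the continuous figures above are conditional.

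It is also fair that no main conclusion depends on these tests. Effects on primary and secondary outcomes have their own sentence and are compared between arms, and no objective is worded as a within-arm change. The error is also conservative under positive correlation, so a reader who inferred a risk of false claims of benefit would have the direction wrong.

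A reader might further infer that the plan intends to read a change significant in one arm only as a treatment effect. The protocol proposes no such inference. Calling within-arm results descriptive is sound practice but does not correct a stated error.

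Finally, the size of the power loss rests on assumed inputs, and the gap is smaller against exact McNemar than against the uncorrected test. Both points stand, though at each assumed correlation chi-square remains the weaker test.

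None of this rescues the categorical part. Chi-square and Fisher's exact are the only categorical tests in the list.

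**Conclusion.** The point holds for categorical pre/post comparisons: the tests assigned assume independence that the visit schedule rules out. The p-values would be conservative, with a true type I error of about 1.9 / 0.6 / 0.03% instead of 5%. In the example the loss of power runs from 6 points (exact McNemar, correlation 0.3) to 56 points (uncorrected McNemar, correlation 0.7). These sizes assume 97 completers in an arm, positive within-person correlation of 0.3 to 0.7 and, for power, a change from 40% to 28%. Neither the correlation nor the change is in the protocol.

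For continuous variables the finding is only that the type of ANOVA should be named. Severity is minor.

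**What to change.** Split the sentence in Analysis of Variable(s).

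- **Between the randomised arms:** keep chi-square, Fisher's exact and ANOVA.
- **Pre/post, categorical:** McNemar's test for binary variables; Stuart-Maxwell or Bowker for more than two categories.
- **Pre/post, continuous:** a paired t-test, repeated-measures ANOVA or a mixed model, named explicitly.
- **Interpretation:** report within-arm changes as descriptive, and draw conclusions on effect from the between-arm contrast.

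The cost is two sentences in the protocol or the statistical analysis plan. No new data, visits or participants are needed.
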